#### Baseline measurement

The baseline questionnaire includes socio-demographic characteristics (age, gender, marital status etc.), the complaint history, all primary and secondary outcomes and patient expectation. Patient expectation will be assessed with the 10-point scale Credibility/Expectancy Questionnaire (CEQ) [34,35].

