### Sample size

Using a power of .9, alpha .05 and a correlation of .5 for repeated measurements, a total of 85 patients per group are needed to detect a clinically relevant mean difference of two points on the NRS for pain intensity (SD 4) [55]. This difference of two points as Minimal Important Change in the NRS is based on a recent review [55]. Anticipating potential study withdrawal (20%) 102 patients per group or 204 patients per randomized comparison are needed. In total, 816 patients need to be included in the four trials.

Through an ‘educated guess’ a SD of four was chosen, because no SD can be found in the literature. Though arbitrary, it is believed conservative, and will ensure that enough patients will be included to find clinically relevant effects, if present.

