### Statistical analysis

Baseline data will be presented comparing the two treatment groups. Intention-to-treat analysis will be conducted for each follow-up moment. Missing data will be imputed with multiple imputation techniques [56,57]. The 95%-confidence intervals will be calculated for the difference of percentages (Chi-square distribution) and means (T-distribution) for dichotomous and continuous outcome variables, respectively. In case of unequal distributions of prognostic factors, multivariate analysis techniques will be used to correct for these between-group differences in prognosis. Multilevel analyses will be performed, with patient, pain clinic, and time of measurement as levels. The threshold of statistical significance is set at *p* < 0.05. Characteristics of patients with missing follow-up data will be compared to those with complete data to identify possible selective drop-out.

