### Economic evaluation from a societal perspective

The economic evaluation will be performed according to the intention-to-treat principle and from a societal perspective. Costs of the minimal interventional procedures, physiotherapy, other health care utilization, patient and family costs, and costs of production losses will be measured and valued. Data are collected through self-completed cost questionnaires.

Missing costs and effect data will be imputed using multiple imputation according to the Multivariate Imputation by Chained Equations procedure corrected and accelerated (Bca) bootstrapping with 5000 replications will be used to estimate confidence intervals around differences in total costs between treatment groups [58,59].

A cost-effectiveness and a cost-utility analysis will be performed. Incremental cost-effectiveness ratios will be calculated by dividing the difference in mean costs by the difference in the mean effects of the two treatment groups. Using a primary clinical effect measures of the trial, for instance pain intensity. Cost-utility will be based on the EQ-5D and expressed in costs per QALY. Uncertainty surrounding incremental cost-effectiveness and cost-utility ratios will be estimated using bootstrapping techniques and graphically presented in cost-effectiveness and cost utility planes. Cost-effectiveness acceptability curves and net monetary benefit will also be estimated. Sensitivity analyses on the most important cost drivers will be performed in order to assess the robustness of the results.

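### The cost-utility analysis specifies no adjustment of the incremental QALY for baseline EQ-5D, which costs precision that the collected data could supply

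*Protocol article*

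**What the plan says.** The protocol article, section Economic evaluation from a societal perspective, sets the ratio as "dividing the difference in mean costs by the difference in the mean effects of the two treatment groups". On the utility side, "Cost-utility will be based on the EQ-5D and expressed in costs per QALY". For precision, "Uncertainty surrounding incremental cost-effectiveness and cost-utility ratios will be estimated using bootstrapping techniques". The section restates intention-to-treat and multiple imputation but names no covariate. Its sensitivity analyses concern cost drivers.

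Baseline utility will be available. The section Baseline measurement says that the first questionnaire holds "all primary and secondary outcomes and patient expectation", and Table 1 marks EQ-5D at baseline and at all six follow-up times.

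The only adjustment rule in the article is in Statistical analysis: "In case of unequal distributions of prognostic factors, multivariate analysis techniques will be used to correct for these between-group differences in prognosis". The economic section neither repeats it nor refers to it.

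**The concern.** A QALY over 12 months is normally the area under the utility curve. The article does not state its construction, but the Table 1 schedule fits this one. Baseline utility is then the first point of the area and is correlated with every later point. An arm that by chance starts with better utility will tend to accrue more QALYs whatever the treatment does. A plain difference in means leaves this chance component in the estimate, and conditioning on baseline EQ-5D removes it.

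Cost-effectiveness is part of the stated aim, and the results are meant to inform reimbursement policy. Four ratios are planned, each exposed to its own baseline imbalance. The sample size is based on pain intensity alone, so no stated calculation secures the precision of the QALY difference.

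**Working it through.** **1. The plan's own figure.** The sample size section says "Using a power of .9, alpha .05 and a correlation of .5 for repeated measurements" and arrives at 85 per group for a difference of 2 NRS points with SD 4. A plain two-sided comparison of two means gives

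n = 2 × (1.960 + 1.282)² × 4² / 2² = 84.06, rounded up to 85 (power at 85: 0.903).

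The figure reproduces. It concerns pain. The article gives no SD and no correlation for EQ-5D, so both are assumed below.

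**2. Inputs.**
- Visits (Table 1): 0, 3, 6, 13, 26, 39 and 52 weeks.
- Group size (Sample size): 102 randomised, or 85 after withdrawal.
- Assumed: QALY by the trapezoid rule, the same EQ-5D SD at every visit, and an equal correlation ρ between any two visits. The central ρ of 0.5 is borrowed from the pain calculation; the range is 0.3 to 0.7.
- Assumed for absolute figures only: EQ-5D SD 0.25, range 0.20 to 0.30.

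**3. Weights.** Each visit's weight is half the time between its neighbouring visits, in years: 0.0288, 0.0577, 0.0962, 0.1923, 0.25, 0.25, 0.125. They sum to 1, and their squares sum to 0.1910.

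**4. Formulas, in units of SD².**
- Var(QALY) = ρ + (1 − ρ) × 0.1910
- Cov(QALY, baseline) = ρ + (1 − ρ) × 0.0288. Because the baseline variance is 1 in these units, this is also the slope of QALY on baseline utility, the share of a baseline difference that passes into the QALY difference.
- R² = Cov² / Var
- Unadjusted SE / adjusted SE = 1 / √(1 − R²)

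At ρ = 0.5: Var = 0.5 + 0.5 × 0.1910 = 0.5955; Cov = 0.5 + 0.5 × 0.0288 = 0.514; R² = 0.514² / 0.5955 = 0.444; SE ratio = 1 / √0.556 = 1.34.

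| ρ | Share passed through | R² | SE ratio |
|---|---|---|---|
| 0.3 | 0.32 | 0.24 | 1.14 |
| 0.4 | 0.42 | 0.34 | 1.23 |
| 0.5 | 0.51 | 0.44 | 1.34 |
| 0.6 | 0.61 | 0.55 | 1.50 |
| 0.7 | 0.71 | 0.66 | 1.72 |

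**5. Another correlation pattern.** If the correlation decays with time as 0.85 × a^t (t in years, a from 0.3 to 0.7, so 0.26 to 0.60 at 12 months), the SE ratio runs from 1.30 to 1.72. The result does not depend on the equal-correlation pattern.

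**6. Absolute scale at ρ = 0.5 and SD 0.25.**
- 102 per arm: unadjusted SE = 0.25 × √0.5955 × √(2/102) = 0.027; adjusted SE = 0.027 × √0.556 = 0.020.
- 85 per arm: 0.030 and 0.022.
- SD 0.20 and 0.30, 102 per arm: 0.022 against 0.016, and 0.032 against 0.024.
- The chance baseline difference at 102 per arm has SE 0.25 × √(2/102) = 0.035. A difference of that size moves the incremental QALY by 0.514 × 0.035 = 0.018.

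**The case against.** The strongest reply is that the quoted sentence is simply the definition of an incremental ratio. An adjusted arm coefficient is also a difference in mean effects, so the text does not forbid adjustment, and an analysis plan that is not shown may provide it. That much stands. Even so, the article sets out a way of computing the ratio and its uncertainty, and no baseline adjustment is part of it.

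A second reply is that the Statistical analysis section already offers a correction and that Table 1 lists the QALY among the secondary outcomes. The rule may therefore have been meant to cover it; the article does not say. If it does, it is still the weaker device. It gives no criterion for imbalance, is triggered after the data are seen, and yields no precision when the arms look alike.

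Three stronger readings are tempting but not supported:

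- **That baseline EQ-5D goes unused.** In an area under the curve it carries a weight of 0.0288, and nothing excludes it from the imputation model. What is unspecified is adjustment for it.
- **That the planned interval is wrong, or too wide by a known amount.** Randomisation makes the unadjusted difference unbiased, and its interval has valid coverage. The figure of 34% depends on a correlation that the article gives only for the pain calculation.
- **That imbalance would carry a ratio across a decision threshold and adjustment would prevent it.** The article states no threshold and no expected QALY gain, and the procedure price it quotes is not an incremental societal cost. With the assumptions above, the sampling error left after adjustment (SE 0.020) is about as large as the shift from a one-SE baseline imbalance (0.018).

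**Conclusion.** The point holds as a matter of efficiency. The economic section specifies no adjustment of the incremental QALY for baseline EQ-5D, although the data will be there, and the conditional rule elsewhere is not tied to it. The unadjusted standard error is about 14% to 72% larger than the adjusted one for an assumed EQ-5D correlation of 0.3 to 0.7. At 0.5 it is 34% larger, and adjustment is then worth 1 / 0.556 = 1.8 times the patients for the QALY difference. About half of a chance baseline difference passes through (0.32 to 0.71 over the same range).

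These figures rest on trapezoid QALYs at the Table 1 visits, equal SDs and complete data. They apply to the QALY difference only. The gain for the acceptability curve and net monetary benefit also depends on cost variance and the cost-effect correlation, for which the article gives no figures. This is a free improvement, not the correction of a biased analysis.

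**What to change.** In the economic evaluation section, or in the analysis plan to which it defers:

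- Define the incremental QALY as the arm coefficient from a regression of QALYs on arm and baseline EQ-5D, whether or not the arms look balanced.
- Refit this regression in every bootstrap replicate jointly with the cost equation, on the same resampled patients, so that the cost-effect correlation is kept.
- Base the ratio, planes, acceptability curve and net monetary benefit on these estimates, and give the unadjusted difference as a secondary figure.
- Include baseline EQ-5D in the imputation model, so that it matches the analysis model.

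The cost is a few sentences and one regression inside a bootstrap that is already planned. No new data, visits or patients are needed.

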## Discussion

The importance of this study is emphasized by the fact that a recent report did not show consensus regarding the effectiveness of minimal interventional procedures for low back pain [60]. This is primarily due to the lack of RCTs with a low risk of bias and an adequate sample size. Conversely, minimal interventional procedures are widely used by anaesthesiologists. Recently published clinical guidelines of the Dutch Society of Anaesthesiologists recommend minimal interventional procedures for a subgroup of patients with low back pain: patients with mechanical low back pain [11]. The decision whether reimbursement of minimal interventional procedures in the Dutch public health insurance system should be continued needs to be made based upon scientific evidence. At this moment it is unclear whether reimbursement should be stopped for the whole group or continued for the subgroup of patients with mechanical low back pain. These four RCTs, including an economic evaluation are designed to provide in this lacking information.

At present, one of the applicants of this study protocol supervises three randomised, double-blind trials that evaluate the efficacy of 1) radiofrequency denervation of the first ramus dorsalis at L3, L4, L5 and S1 in patients with facet joint pain, of 2) radiofrequency denervation of the ramus communicans in patients with intervertebral disc pain, and of 3) radiofrequency denervation of the ramus dorsalis at L5, S1, S2 in patients with SI joint pain. These three trials are placebo controlled and do not include economic evaluations. The current trials will be the first on this topic including an economic evaluation.

We did not choose to perform placebo-controlled experiments. However, because of the nature of the study, it was not desired to perform a placebo-controlled study either [61]. Furthermore, both the ethics and feasibility of performing placebo injections are currently under debate [62,63]. In our study it will not be possible to determine to what extent any observed benefits of the minimal interventional procedures are attributable solely to its placebo effect, which can be considered a limitation of this trial. The pragmatic nature of our RCTs mirrors daily practice which will improve the generalizability [64].

Based on clinical experience we hypothesize that for patients with chronic mechanical low back pain, a multidisciplinary pain programme with minimal interventional procedures will be more effective than a programme without these procedures. The main expected effect is short-term pain reduction, but it is likely that this will be associated with improved functioning and quality of life. The costs of minimal interventional procedures are approximately (depending on the treating hospital and the health insurance company) between €2500,- and €3500,- per treatment [65]. We expect that the average costs of patients who receive minimal interventional procedures are higher than those of patients in the control group. However, if clinical outcomes are better minimal interventional procedures may be cost-effective if the incremental costs are worthwhile. Also, improved clinical outcomes and more rapid recovery might result in less additional health care consumption and lower costs of work absenteeism and consequently in lower additional costs.

This study will provide more knowledge on the treatment of chronic mechanical low back pain. Furthermore, results of this project will be included in future updates of the clinical guidelines of low back pain. The Dutch Association of Anaesthesiology supports this project and will use the results in a future update of their clinical guidelines. Finally, the results of this study will inform governmental policy regarding reimbursement of minimal interventional procedures for chronic mechanical low back pain. The results of the trials are expected to be available at the end of 2015.

## Abbreviations

RCT: Randomized controlled trial; SI-joint: Sacroiliac joint; CVZ: Health insurance council; IASP: International association for the study of pain; ISIS: International spinal injection society; 4DSQ: Four-dimensional symptoms questionnaire; CPAQ: Chronic pain acceptance questionnaire; HADS: Hospital anxiety depression scale; PCI: Pain coping inventory; PCL: Pain cognition list; L: Lumbar vertebrae; IDET: Intradiscal electrothermal therapy; QALY: Quality adjusted life years; CEQ: Credibility/expectancy questionnaire; NRS: Numerical rating scale; ODI: Oswestry disability index; EQ-5D: EuroQol; MPI: Multidimensional pain inventory; PRODISC: Productivity and disease questionnaire; SD: Standard deviation.
